## Background

Generally, knee osteoarthritis (KOA) is the most common cause of knee pain and dysfunction in the elderly. Osteoarthritis usually affects the medial compartment of the knee joint, which is related to misalignment. Currently, most research has focused on the treatment of pain relief and prevention of decline in function [1, 2].

Autologous platelet-rich plasma (PRP) is a safe autologous blood product containing high levels of growth factors and cytokines with potential to alter biological processes implicated in OA pathogenesis and symptoms [3]. In addition, several studies have reported that compared with non-steroidal anti-inflammatory drugs (NSAIDs), steroid and hyaluronic acid, PRP has favorable pain and function outcomes, [4–6] suggesting the potential benefits of PRP in treating KOA. Some alternative physical therapy, such as low-level laser therapy, needs to be further confirmed for efficacy in KOA patients [7].

Recent systematic reviews concluded that platelet dysfunction might have an impact on the efficacy of PRP [8]. For certain patients with hematological diseases (e.g. immune thrombocytopenia, aplastic anemia, systemic lupus erythematosus, etc.) and patients receiving anti-platelet medications, autologous PRP is not an optimum solution. Allogeneic platelet-rich plasma has been shown to be safe and effective in treating osteoarthritis, rotator cuff dysfunction, refractory wounds, and other medical fields [9–12]. Given the clinical effect on pain reduction in osteoarthritis and a good safety profile, allogeneic PRP is a promising nonsurgical therapy for knee OA combined with hematologic blood dyscrasias with platelet dysfunction. However, clinical trials of efficacy to date have been limited by a high risk of bias in allogeneic PRP trials. Although the results show that allogeneic PRP is safe and can relieve pain and recover articular function, the trials lack adequate blinding and control group suggesting the results are not convincing [11, 12]. Well-designed and long-term follow-up prospective randomized controlled trials (RCTs) have not yet been performed.

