**Other measures**							
**Drug/supplement use**		**×**		**×**	**×**	**×**	**×**
**Platelets and leukocytes counts, VEGF and TGF-β**			**×**				
**Number of injections**			**×**				
**Adverse events**			**×**	**×**	**×**	**×**	**×**
**Success of blinding**			**×**				

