### Randomization procedures

Randomization is centralized, and participants will be randomly allocated in a 1:1 ratio. An independent statistician will provide a computer-generated randomization list, using a permuted block design with block sizes of 4 and 6. The sequence is concealed by the use of a computer interface implemented in the electronic case report form. The patients, treating physicians and coordinating researchers will all be blinded to the allocation of the intervention. A study nurse will have access to the randomization result and the allocated intervention.

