### Interventions

Participants in both the allogeneic PRP and saline groups will receive one intra-articular knee injection at the same time after signing written informed consent (supplement 3), in line with commonly used injection protocols for this condition [6, 15]. The study nurse will give the treating physician an occluded syringe with a needle containing 4 ml of either normal saline or allogeneic PRP, and the contents will be injected into the knee joint. After the injection, passive knee flexion and extension will be performed six times with the participant observed resting for 20 min thereafter.

After injection, participants will be asked which group they believe they are in, and separately the injecting treating physician will also be asked which group they believe the participant is in to assess the success of blinding. This will be registered accordingly. The study nurse will ask the participant if they experienced any adverse events following the injection.

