### Sample size calculations

The sample size calculation is based on the primary outcome measure, the WOMAC score at 12-month. Based on previous studies, [5, 16, 17, 25] a 11.5 points reduction in WOMAC total score was considered as the minimum difference to be detected between the groups with a standard deviation (SD) of 16. Accepting a false-positive rate of 5% (α = 0.05) and a power of at least 90% (β = 0.10), we determined a theoretical minimum sample size of 84 patients. Considering the estimated 15% dropout rate, a total of 50 patients per group were required. Patient recruitment will be terminated in both groups when the required minimum number of patients is attained.

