### Secondary outcomes analysis

To test for the effect of treatment on between-group differences in secondary outcomes, we will also use the repeated measurement general linear model (GLM) with the Sidak test for multiple comparisons. Changes from baseline to all follow-up time points will also be included in the model. The statistical analysis method is similar to the primary analysis. MRI-derived measurements will be compared between groups using appropriate models, adjusting for age, sex, body mass index, and the stratifying variables. The success of blinding will be assessed using the James Blinding Index [26].

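### The one blinding measure named, the James index, pools the arms and can miss unblinding confined to one arm; an arm-specific index from the same guesses would show it

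*Protocol article*

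**What the plan says.** - Protocol article, Secondary outcomes analysis: "The success of blinding will be assessed using the James Blinding Index". This is the only blinding analysis the article names. It gives no cut-off for success and ties no efficacy decision to the result.
- Protocol article, Interventions: once the injection has been given, "participants will be asked which group they believe they are in". The physician who injected gives a guess of their own for each participant. The answers are recorded. Whether don't know is an allowed answer is neither stated nor excluded.
- Protocol article, Table 1: the row "Success of blinding" is marked at the injection visit only.
- Protocol article, Background: of earlier allogeneic PRP studies the authors say that "the trials lack adequate blinding and control group suggesting the results are not convincing".

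**The concern.** The James index condenses both arms into one number and gives don't-know answers full credit as blinding. If recognition of the product were confined to the PRP arm, the saline arm would dilute it, and don't-know answers in either arm would raise the index further. The result could look satisfactory while one arm knew its allocation.

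This matters because WOMAC, the primary outcome, is completed by the patient and can move with expectation. The article also faults earlier work for weak blinding, so readers will look to this check for reassurance. The guesses needed for an arm-specific index are already to be collected.

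**Working it through.** **Inputs.** The article gives no figure for the blinding index and no guess rates, so every response pattern below is an assumption. The one input taken from the plan is 50 patients per group (Sample size calculations; 1:1 allocation in Randomization procedures). That figure reproduces: a two-sided t test at 0.05 with difference 11.5 and SD 16 has power 0.902 at 42 per arm, which is 84 in total, and 42 / 0.85 = 49.4, rounded up to 50.

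**Formulas.**
- James index = [1 + P_DK + (1 − P_DK) × K_D] / 2, where P_DK is the don't-know share and K_D = (observed − expected disagreement) / expected disagreement among those who guess. It is 0 for complete unblinding, 0.5 for random guessing with no don't-know answers, and 1 if everyone answers don't know.
- Bang index, per arm = (correct − wrong) / n, with variance (p_correct + p_wrong − index²) / n.
- When equal numbers guess in each arm, as in every row below, expected disagreement is 0.5 and the James index reduces to P_DK + P_wrong, that is, 1 minus the overall proportion correct. A don't-know answer then counts exactly as a wrong guess does.

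**First row in full.** PRP 25 correct, 5 wrong, 20 don't know; saline 15, 15, 20. P_DK = 40/100 = 0.40. Observed disagreement = (5 + 15)/60 = 0.333. K_D = (0.333 − 0.5)/0.5 = −0.333. James = [1 + 0.40 + 0.60 × (−0.333)]/2 = 0.60. PRP Bang = (25 − 5)/50 = 0.40, with standard error √[(0.60 − 0.16)/50] = 0.094.

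**Results at 50 per arm** (correct/wrong/don't know; 95% intervals by multinomial resampling for James, Wald for Bang):

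| Pattern | PRP arm | Saline arm | James | Bang, PRP | Bang, saline |
|---|---|---|---|---|---|
| One arm, with don't know | 25/5/20 | 15/15/20 | 0.60 (0.51 to 0.69) | +0.40 (0.22 to 0.58) | 0.00 (−0.21 to 0.21) |
| Forced choice, strong | 40/10/0 | 25/25/0 | 0.35 (0.26 to 0.44) | +0.60 (0.38 to 0.82) | 0.00 (−0.28 to 0.28) |
| Forced choice, moderate | 33/17/0 | 25/25/0 | 0.42 (0.33 to 0.52) | +0.32 (0.06 to 0.58) | 0.00 (−0.28 to 0.28) |
| Forced choice, random | 25/25/0 | 25/25/0 | 0.50 (0.40 to 0.60) | 0.00 (−0.28 to 0.28) | 0.00 (−0.28 to 0.28) |
| Forced choice, both arms lean to PRP | 40/10/0 | 10/40/0 | 0.50 (0.42 to 0.58) | +0.60 (0.38 to 0.82) | −0.60 (−0.82 to −0.38) |

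**Dependence on don't-know answers.** Suppose 80% of PRP guessers and 50% of saline guessers are correct, with the same don't-know share d in each arm. The overall proportion correct is 0.65 × (1 − d), so James = 1 − 0.65 × (1 − d): 0.35 at d = 0, 0.48 at 20% and 0.61 at 40%. It crosses 0.5 at d = 1 − 0.5/0.65 = 0.23. The PRP Bang index, 0.60 × (1 − d), is 0.60, 0.48 and 0.36 at the same three points.

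**Reading.** In the first row the James interval lies wholly above 0.5 although the PRP-arm interval excludes 0. In the third row the James interval spans 0.5 although the PRP-arm interval excludes 0. In the second row the James index does its job. The last two rows give the same James value from different behaviour, and only the arm-level values separate them.

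**The case against.** The strongest reply is that this is a preference between methods. The James index is established, the check is supportive, and no estimate or test depends on it. That stands: naming it is neither an error nor a contradiction.

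A second reply is that the article is condensed, and a fuller protocol or analysis plan may add a table by arm or an arm-specific index. That also stands. The point can only be that this is the one measure named here.

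A third reply is that the clearest masking example needs many don't-know answers, and the article does not say they are allowed. This is partly right. Without them, strong one-arm unblinding is detected, as the second row shows. Moderate unblinding can still escape, although in that row the saline interval (−0.28 to 0.28) is wide enough that a shared lean towards PRP cannot be ruled out.

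Two stronger readings are tempting, and the document supports neither:
- A reader might infer that, if guesses are forced, the index cannot show success because random guessing gives 0.50 and not 1. But 0.5 is the reference for random guessing, and unblinding is inferred when the interval lies below it. A value of 0.50 (0.40 to 0.60) shows no evidence of unblinding.
- A reader might infer that PRP-arm unblinding is likely. The article describes preparation in a separate room, an opaque label over syringe and needle base, equal 4 ml volumes and donor blood, so no draw for PRP marks out the PRP patients. One-arm unblinding is a possibility to check for, not an expectation.

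**Conclusion.** The point holds as a minor, inexpensive improvement. A pooled James index can stay at or above 0.5, or have an interval that includes 0.5, while the PRP arm alone is unblinded: 0.60 against a PRP Bang index of +0.40 with 40% don't-know answers, and 0.42 against +0.32 under forced choice. It does not miss strong one-arm unblinding under forced choice (0.35, upper limit 0.44).

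These sizes rest on assumed guess rates, 50 responders per arm and 0.5 as the conventional reference, since the article sets no threshold. The conclusion concerns how the blinding result is interpreted; the primary analysis is untouched.

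**What to change.** 1. Before any answers are collected, fix the response options as PRP, saline or don't know. A don't-know answer cannot be recovered later from a forced guess.
2. Tabulate guesses by allocated arm, separately for participants and for injecting physicians.
3. Report the Bang index per arm with its 95% confidence interval beside the James index.
4. State in advance how the two arms will be read together. A PRP-arm interval wholly above 0 with a saline value near 0 points to unblinding in the PRP arm and would be reported as a limitation on the WOMAC result. A positive PRP value with a saline value equally far below 0 points to optimistic guessing in both arms, not unblinding.

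The cost is one response box on a question already asked, a few lines of analysis and one more index to report.

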### Ethics and dissemination

The trial will be conducted according to the principles of the Declaration of Helsinki. Ethical approval has been obtained from the National Clinical Research Center for Hematologic Disease, the First Affiliated Hospital of Soochow University Ethics Committee (No.2021–356). The trial has been registered in the Chinese Clinical Trial Registry (ChiCTR2100048624) and any revisions about the protocol are documented in this registry. All participants will provide written informed consent before any study-related procedures.

The results of the trial will be reported first to trial collaborators. The main report will be drafted by the trial coordinating team, and the final version will be agreed upon by the Trial Steering Committee before submission for publication, on behalf of the collaboration.

The results of this trial will substantially inform clinical practice on the clinical effectiveness and safety of the treatment in these patients. The results of this project will be disseminated through peer-reviewed journals, conference presentations, the National Library for Health and through local mechanisms at the participating center.

## Discussion

This is a prospective, randomized, double-blind, placebo-controlled trial evaluating the efficacy and safety of intra-articular injection of allogeneic PRP from blood donors in patients with knee OA combined with hematologic blood dyscrasias with platelet dysfunction who are unsuitable for autologous PRP therapy. The primary outcome is the WOMAC score at 12-month. Our study will also evaluate the long-term efficacy of allogeneic PRP for up to 5 years.

Autologous PRP has been shown to alleviate the symptoms of patients suffering from knee OA and allogeneic PRP has been proven to be safe and effective in the treatment of osteoarthritis, rotator cuff disease, refractory wounds and other medical fields [3, 9–12]. In the absence of effective evidence-based non-surgical interventions for patients with knee OA combined with hematologic diseases with platelet dysfunction, allogeneic PRP would fulfill a clear clinical need. There was only one preliminary study on the efficacy of allogeneic PRP for knee OA with short follow-up periods, no control group, and low evidence [12]. In addition, all PRPs used for injection in the present study are from the same healthy donor at the same time and prepared with the same system. This avoids confounding factors and high risk of bias.

A positive study outcome is that allogeneic PRP could be used as a non-surgical intervention to treat patients with knee OA who are unsuitable for autologous PRP therapy. A negative outcome will prevent the widespread use of a non-efficacious treatment.

This study has potential limitations. First, the generalizability of results to other PRP products and treatment regimens remains unknown. All PRP products differ in their production method and content, and different treatment regimens regarding dose, timing and number of injections are used in clinical practice. However, we prepare PRP using commercial kits by standardized procedures and analyzed related components. Second, this study will not control for variations in physical therapies between the two groups. Throughout the trial, the exercise therapy and lifestyle will be registered. Third, the population recruited is from a single center. However, as our center is one of the three national clinical research centers for hematologic disease in China, it will help us screen a homogenous group of participants better.

## Data Availability

All data will be used only for analysis of the present study and will be protected from any unnecessary exposure. All information will be published confidentially, without the name of the subjects exposed. All data will be available for review and confirmation of data analysis when requested by a review process for publication of the article in indexed scientific journals or presentations at scientific events.

## Abbreviations

SPIRIT: Standard Protocol Items: Recommendations for Interventional Trials
CONSORT: Consolidated Standards of Reporting Trials
WOMAC score: The Western Ontario and McMaster Universities Osteoarthritis Index
VAS: Visual analogue scale
SF-36: The short-form 36 item health survey questionnaire
MOAKS: Magnetic resonance imaging Osteoarthritis Knee Score
MRI: Magnetic resonance imaging
KOA: Knee Osteoarthritis
RCT: Randomised controlled trial
